### Study Setting

The main study setting will be remote and will involve near real-time home-based monitoring, and data will principally be collected under this setting. Participants will also attend baseline and exit face-to-face visits with the clinical team, during which initial baseline and exit data will be obtained and assessments will be conducted.

### Sample and Recruitment

#### Inclusion Criteria

The inclusion criteria are presented in Table 3.

**Table 3 table3:** Inclusion criteria.

Criteria	COPD^a^	ILD^b^	PH-COVID^c^
Clinical conditions	20 patients with a diagnosis of COPD	20 patients with a diagnosis of ILD	A clinical diagnosis of COVID-19 (within 4-13 weeks of enrollment) who report symptoms interfering with day-to-day activity present for more than 28 days following the onset of COVID-19
Gender	Male/Female	Male/Female	Male/Female
Age range (years)	18+	18-90	18+
Prior mobile phone use	Required	Required	Required
Willingness to use monitoring devices and complete study questionnaires	Required	Required	Required
History of exacerbation	2 or more exacerbations in the last 1 year	N/A^d^	N/A

^a^COPD: chronic obstructive pulmonary disease.

^b^ILD: interstitial lung disease.

^c^PH-COVID: posthospitalization COVID.

^d^N/A: not applicable.

#### Exclusion Criteria

The exclusion criteria for all groups (COPD, ILD, and posthospitalization COVID) are as follows: non-English language speaker, lack of physical capability to participate (eg, heart failure), pregnancy, and lack of capability to consent.

### Sampling

Convenient sampling will be employed for this pilot study.

#### Sample Size

The study will include 20 participants for each of the three disease areas. This is a small sample feasibility study to assess the practical use of remote monitoring in three lung disease areas. The sample size will adequately allow objective assessment of the system deployed for this type of data collection in the typical patient population.

#### Sampling Technique

Sequential participants who fit the inclusion/exclusion criteria will be identified from the respiratory outpatient clinics at the University College London Hospital (UCLH) and Royal Free Hospital (RFH).

### Recruitment

Participants who fit the inclusion/exclusion criteria will be identified from the respiratory outpatient clinics at the UCLH and RFH.

### Sample Identification

#### Participant Search and Consent

Recruitment will be done either in person (via a cleanroom) or remotely (by phone or video call) by clinicians, who will provide information about the study in an easily accessible form reviewed by the patient advisory board. As part of the consent process, participants will be informed that the data they provide will not be actionable (in other words, it will not trigger a clinical investigation or intervention). Written informed consent will be obtained prior to performing any study assessments or procedures. Participants will be requested to consent to their medical records being made available to the study team throughout the study.

#### Participant Cohorts

##### ILD/IPF

The ILD/IPF cohort will include 20 participants recruited from the UCLH ILD service followed for 6 months. We will recruit patients across the spectrum of progressive to stable disease. We will analyze whether monitoring is able to detect progression earlier than the current standard (lung function test performed every 3 months or patient reporting to a clinician) and could help us identify progression earlier.

##### COPD

We will recruit 20 patients with COPD from our services in London and follow them for up to 6 months or until the first exacerbation, whichever is sooner. We will recruit patients with a history of exacerbations to increase the likelihood of identifying patients who would experience events during the study. We will analyze whether monitoring is able to detect exacerbations earlier than the current gold standard (patient reporting to a clinician) and therefore could be used to help patients get treatment earlier.

##### Posthospitalization COVID

For UCLH participants, we will define the population under study as people with a clinical diagnosis of COVID-19 (within 4-13 weeks of enrollment) and who report troublesome symptoms interfering with day-to-day activity present for more than 28 days following the onset of COVID-19 (n=20). A baseline assessment will be conducted remotely via a web-based questionnaire, which will obtain information on demographics, medical and psychiatric history, health behaviors, and medications. Participants will be asked about the symptoms, severity, and consequences (eg, hospitalization and ventilatory support) of their acute illness.

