**Methods:**

Twenty participants will be recruited in each of three cohorts (COPD, IPF, and posthospitalization COVID). Data collection will be done remotely using the RADAR-Base (Remote Assessment of Disease And Relapse) mobile health (mHealth) platform for different devices, including Garmin wearable devices and smart spirometers, mobile app questionnaires, surveys, and finger pulse oximeters. Passive data include wearable-derived continuous heart rate, oxygen saturation, respiration rate, activity, and sleep. Active data include disease-specific patient-reported outcome measures, mental health questionnaires, and symptom tracking to track disease trajectory. Analyses will assess the feasibility of lung disorder remote monitoring (including data quality, data completeness, system usability, and system acceptability). We will attempt to explore disease trajectory, patient stratification, and identification of acute clinical events such as exacerbations. A key aspect is understanding the potential of real-time data collection. We will simulate an intervention to acquire responses at the time of the event to assess model performance for exacerbation identification.

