### ILD

ILD, or lung fibrosis, is one of a spectrum of fibrotic diseases associated with aging, obesity, diabetes, and pollution, which are responsible for approximately 45% (9/20) of premature deaths in Western Europe. Of over 90,000 patients in the United Kingdom with ILD, approximately 30,000 have idiopathic pulmonary fibrosis (IPF), which is the most severe form. IPF is a disease of unknown etiology that is more frequent in males and presents mainly in the sixth and seventh decades of life [5]. There is no cure, and the median survival of 3 to 5 years following diagnosis is worse than that for many cancers. As the fibrosis progresses, there is impaired pulmonary function, respiratory failure, and ultimately death. Throughout its course, IPF has significant effects on physical (dyspnea, dry cough, weight loss, and fatigue) and social (recreational activities and relationships) functions, with severe consequences for the patient’s health-related quality of life (QoL). Clinical courses are punctuated by episodes of worsening disease that may result in death. These acute exacerbations of IPF (AE-IPF) are estimated to occur in 4% to 20% (1-4 in 20) of patients each year, but the true incidence and impact are not known [6].

Management of AE-IPF involves establishing the diagnosis and excluding other causes of increasing dyspnea, excluding infection, and considering the use of steroids, antibiotics, and/or anticoagulation, none of which has been shown to be of benefit. The trajectory of patients with IPF is heterogeneous with great variability in the disease course. Some progress slowly, whereas others progress more rapidly, and this can cause emotional distress and anxiety. Patient-reported outcome measures are used to measure health-related QoL, assess symptoms, and evaluate disease progression. The management of patients with IPF is multifaceted and consists of patient education and support, regular outpatient surveillance, symptom relief, pulmonary rehabilitation, annual vaccinations to prevent respiratory infection, identification and management of AE-IPF, supplemental oxygen, management of comorbidities, and ultimately palliative care or, in a minority of patients, referral for lung transplantation [7].

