### Aims

Our goal is to investigate the acceptability and feasibility of remote monitoring of patients with pulmonary disorders for the quantification of symptoms, understanding of the disease trajectory, and detection and prediction of clinically important events, such as exacerbations, in the following three disorder areas: COPD, ILD, posthospitalization COVID.

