#### Assess the Potential of Remote Monitoring in COPD, IPF, and COVID-19

The potential of remote monitoring will be evaluated in the context of cardiopulmonary disorders. This will involve developing methods to quantify disease trajectory as compared with standard clinical measures (in IPF, these would be changes in forced vital capacity and death); detecting exacerbations/symptoms, such as changes in wearable data (eg, HR, SpO_2_, and activity), during the reported period of exacerbation (a real-time algorithm will be included to predict exacerbations with patients notified with the ERS to confirm the prediction at or close to the time of the event); detecting exacerbations prior to or after the reported period of exacerbation (eg, a signal that may precede participant awareness of the exacerbation/symptom); detecting subclinical exacerbations in patients with lung fibrosis; tracking self-reported symptoms and outcomes (including precursor presymptomatic signals) and their frequency and order; and reporting longitudinal mental health symptom measures, as reported by the Generalized Anxiety Disorder scale (GAD-7) and Patient Health Questionnaire depression scale (PHQ-8), associated with the three diseases. This will provide the potential to assist with future applications around disease self-management. In the case of the posthospitalization COVID cohort, we will assess whether remote monitoring can be used as a symptom collection tool and as a long-term low-burden monitoring solution. Fatigue will be assessed by Garmin Body Battery values and the Fatigue Severity Scale, while long-term COVID impairments will be measured weekly using the Centers for Disease Control and Prevention (CDC) COVID-19 long-term effects (CCLTE) list, World Health Organization (WHO) symptoms list, and post-COVID functional status (PCFS), a COVID-19-specific widely used questionnaire on health-related impairments (physical functioning scale).

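### The posthospitalization COVID cohort has no hospitalization criterion, so never-admitted patients qualify; the ILD/IPF cohort name also needs reconciling

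*Protocol article*

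**What the plan says.** **COVID cohort.** The abstract states: "Twenty participants will be recruited in each of three cohorts (COPD, IPF, and posthospitalization COVID"). The Aims list the same label, "in the following three disorder areas: COPD, ILD, posthospitalization COVID". The Introduction section on this cohort rests its case on follow-up after a hospital stay and on the unknown needs of people since discharged.

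Eligibility is stated twice. In Participant Cohorts, under Posthospitalization COVID, the article says "we will define the population under study as people with a clinical diagnosis of COVID-19 (within 4-13 weeks of enrollment") and adds troublesome symptoms lasting more than 28 days from onset. Table 3 gives essentially the same rule. Neither mentions admission. The cohort section then describes the baseline questionnaire: "Participants will be asked about the symptoms, severity, and consequences (eg, hospitalization and ventilatory support) of their acute illness".

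**ILD/IPF cohort.** The abstract calls this cohort IPF. So does the outcome section "Assess the Potential of Remote Monitoring in COPD, IPF, and COVID-19", which gives a comparator specific to that disease: "in IPF, these would be changes in forced vital capacity and death". The Aims, the cohort column of Table 2, Table 3, the Exclusion Criteria and Progress to Date say ILD. The cohort's own section says ILD/IPF. The only diagnostic criterion, in Table 3, is "20 patients with a diagnosis of ILD". The Introduction makes clear that the two terms differ: "Of over 90,000 patients in the United Kingdom with ILD, approximately 30,000 have idiopathic pulmonary fibrosis (IPF").

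**The concern.** A cohort's name tells readers whom the results describe; its eligibility criteria decide who enters. For COVID the two disagree. A patient who managed the acute illness at home and still has symptoms meets every stated criterion and would be counted as posthospitalization. Symptom trajectories, functional status and fatigue results from an unknown mix could then be carried to discharged patients, which is the group the Introduction sets out to study.

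The ILD/IPF wording raises a smaller version of the same problem. The IPF comparator, the two questionnaires named for IPF and any count of acute exacerbations of IPF (AE-IPF) refer to a subset of the patients whom Table 3 admits. The Secondary Objective is to inform power calculations on exacerbation numbers, and a rate from an unspecified ILD mix does not carry over to an IPF study.

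**Working it through.** **The plan's own figure.** The target is 20 per cohort, 3 × 20 = 60 in all. The Sample Size section justifies it by feasibility alone, with no alpha, power, effect size or event rate, so there is no calculation to reproduce. The check is a comparison of sections, with a short calculation for the ILD/IPF cohort.

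**COVID: the sections side by side**

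| Place | Requires an admission? |
|---|---|
| Abstract, Aims, outcome section, Table 3 column title | Label only |
| Introduction | Rationale only |
| Table 3, clinical conditions | No |
| Participant Cohorts, Posthospitalization COVID | No |
| Exclusion Criteria (all groups) | Never-admitted patients are not excluded |
| Sampling Technique, Recruitment | No; the source is respiratory outpatient clinics |
| Baseline questionnaire | Asks about hospitalization as one example of a consequence |

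The last row matters most. A question whose answer may be yes or no describes a variable, not an entry condition. The cohort section addresses UCLH participants, but Table 3 gives the same rule without naming a site, so no separate criterion for the other hospital is implied. The article contains no admission rate, so the never-admitted number is bounded only by 0 and 20.

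**ILD/IPF: expected number with IPF**

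Inputs: about 30,000 IPF among over 90,000 ILD patients (Introduction, ILD); n = 20. Assumption: the clinic mix equals the UK mix.

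- Share = 30,000/90,000 = 1/3.
- Expected IPF patients = 20 × 1/3 = 6.7, about 7.
- Central 95% range of Binomial(20, 1/3): 3 to 11.
- Other shares: 25% gives 5, 50% gives 10, 75% gives 15.

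The binomial range covers chance only, not uncertainty about the share. The input is also unsettled in the article: the Introduction gives 30,000 first as existing UK IPF patients and later as diagnoses per year.

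**ILD/IPF: AE-IPF in 6 months**

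Input: 4% to 20% of IPF patients per year (Introduction, ILD). Taking half the annual figure for 6 months gives h = 0.02 to 0.10.

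| | All 20 have IPF | One third have IPF |
|---|---|---|
| Expected patients with an event | 20h = 0.4 to 2.0 | 20h/3 = 0.13 to 0.67 |
| P(no event) | (1 − h)^20 = 67% to 12% | (1 − h/3)^20 = 87% to 51% |

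The expected number falls threefold, but it is small in both columns.

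**The case against.** **On COVID**, the best defence is that the column title in Table 3 supplies the missing condition. That does not hold up well. The COPD and ILD columns restate their diagnosis as a criterion, and the COVID column states a full definition that leaves admission out. One might also expect patients seen in a hospital respiratory clinic to be mostly post-discharge. That is possible, but the article does not say so.

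A fairer point is that the criteria fit the Introduction's other stated aim, observing people with long COVID. The label may therefore be what is wrong, not the criteria. This stands, and it is why renaming must be open as a remedy.

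**On ILD/IPF**, most operative text says ILD, and Table 2 describes both IPF-named questionnaires as ILD quality-of-life reports. The cohort's stated analysis is earlier detection of progression, not AE-IPF counts. The AE-IPF rate appears only as background. Progress to Date reports two exacerbations with eight ILD and one COPD participant enrolled. COPD follow-up ends at the first exacerbation, so at least one event appears to come from the ILD arm, which suggests that events other than AE-IPF may be counted. All of this stands, and it reduces this part to an inconsistency of naming.

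**Stronger readings the documents do not support.** A reader might infer that results could not be stated for either named population. That goes too far: hospitalization is asked at baseline, and medical records are available by consent (Clinical Data), so the actual mix can be described. What is absent is any stated intention to report by it. A reader might also infer that the second cohort will be mostly non-IPF patients reported as IPF. That depends on applying a national ratio to a specialist ILD service, and on overlooking how often the article says ILD.

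**Conclusion.** The COVID part holds on the text alone and needs no assumption. The label and rationale say posthospitalization, the two eligibility statements do not, and no other section closes the gap. Its practical size is unknown: between none and all of the 20. It affects how clinical and symptom findings can be described, and it should be settled before COVID recruitment begins.

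The ILD/IPF part is a lesser, related inconsistency. The figure of about 7 IPF patients in 20 (binomial range 3 to 11; 5 to 15 expected at shares of 25% to 75%) is illustrative and rests on the clinic resembling the UK as a whole. Resolving the name would not rescue an event analysis, since AE-IPF would be few even in a pure IPF cohort, and Limitations already concedes that size and duration may fall short.

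Recruitment, retention, data completeness and the technology survey are little affected by either point.

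**What to change.** **COVID.** Reconcile the sections in one of two ways:

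1. Add a documented hospital admission for COVID-19 to Table 3 and to the cohort section. The cost is probably slower recruitment.
2. Rename the cohort symptomatic post-COVID wherever it is named, adjust the Introduction's rationale, and report results by admission status, using the baseline question already planned. The cost is a narrower claim about posthospitalization patients, resting on however many were admitted.

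The article does not show which was intended, so the choice belongs to the investigators. Progress to Date lists ILD and COPD participants only, so either change can apparently be made before anyone enters this cohort.

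**ILD/IPF.** Name the cohort ILD throughout, including the abstract and the outcome section. Record IPF versus other ILD at baseline. Limit the IPF comparator, conclusions from the IPF-named questionnaires, and AE-IPF counts to the IPF subset. The cost is wording, one baseline field, and IPF-specific statements that rest on fewer patients. Requiring IPF only from now on would not resolve the matter: eight of the 20 are already enrolled under the ILD criterion, so the cohort could still be mixed.

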### Consent

Informed consent will be sought at the end of the screening process and prior to the baseline clinical team meeting. Patients will have the study explained to them and will be given a copy of the participant information sheet (PIS). They will be given adequate time to consider taking part in the study and to ask any questions. Patients who are unable to give informed consent will not be recruited. Due to the nature of the remote monitoring study, we will optionally include a remote consent process for participants who are not able to attend the clinic in person. The remote consent process will be implemented using the REDCap electronic case report form (eCRF) e-Consent module to deliver the consent form; however, it is our preference to seek to keep wet signature/paper-based consent forms. These will be held both as electronic copies and hard copies.

Upon receipt of consent forms, participants will be booked for the enrollment training session. Prior to the session, participants will be provided a RALPMH study pack including study devices (Garmin, spirometer, and finger pulse oximeter) and equipment either by post or during a face-to-face session (via a cleanroom) if possible. Participants will receive a 45- to 60-minute training session on the use of the wearable devices, mobile sensors, and aRMT smartphone app. This will include a PIS leaflet summarizing key information and researcher contact details for future reference. The purposes of the study will be clearly explained, and participants will be provided with practical information, such as how to switch devices on and off, how to charge devices, and how to respond to questionnaires and digital tests on a notification via the app. Participants will receive a follow-up call 1 week after the start of data recording for any additional support as required. If participants do not have a suitable phone, we may provide one from a limited number of reserve devices. Precreated accounts for devices (eg, Garmin) will be registered using a study email address (eg, [contact]) and dummy contact details. Baseline data will be collected in this first session via the study REDCap eCRF project instruments.

## Results

### Study Flow Chart

The study flowchart is shown in Figure 3. At the start of the study, participants remotely consent and are provided with the PIS. They are then provided a set of enrollment or baseline assessments to complete online.

All the scheduled active assessments (self-reports) that need manual input periodically are shown on the left, which are piped through the active data collection app to the RADAR-Base platform.

**Figure 3 figure3:**
[figure not shown]
Study flow diagram. CAT: COPD assessment test; CCLTE: CDC COVID-19 long-term effects; COPD: chronic obstructive pulmonary disease; EoP: experience of participation; ERS: Exacerbation Rating Scale; FSS: Fatigue Severity Scale; GAD-7: Generalized Anxiety Disorder scale; ILD: interstitial lung disease; IPF: idiopathic pulmonary fibrosis; l-IPF: living with idiopathic pulmonary fibrosis; KBILD: The King's Brief Interstitial Lung Disease; MRC: Medical Research Council; PCFS: post-COVID function status; PHQ-8: Patient Health Questionnaire depression scale; PROM: patient-reported outcome measure; PSQI: Pittsburgh Sleep Quality Index; RADAR: Remote Assessment of Disease and Relapse; SGRQ: St. George's Respiratory Questionnaire; TAMF: Technology Acceptance Model Fast Form; VAS: visual analog scale; WCS: World Health Organization COVID-19 symptoms.

The wearable device provided to participants connects to the wearable vendor’s application, and the data are uploaded to the vendor’s server, which is then synchronized to the RADAR-Base platform. On getting all the data, the RADAR-Base platform runs real-time data processing, and based on a threshold for exacerbation, it sends a notification and assessment for confirmation of the exacerbation in the form of the ERS. On exit or completion of the study, the participants will be asked about their experiences with the technology and the study.

### Timeline

The timeline for the study is shown in Figure 4. The planning and technical support for the study were setup in March 2021. The recruitment and data collection phase has started in June 2021 and will end in June 2022 (1 year). At various points during this period, a review of the data quality and quantity will be performed. Data processing and analysis has started in July 2021 and is planned to end in October 2022. The publication writeup and final publication are planned from September 2021 to December 2022.

